### 3. STUDY DESIGN

An RCT with a cost-effectiveness analysis, will be performed in three non-university large teaching hospitals in the Netherlands (Amphia Hospital Breda, Elisabeth Tweesteden Hospital Tilburg and Meander Medical Center Amersfoort), during the period of November 2025 to May 2028. All patients of 65 years or older, with a new onset of CLTI presented at the outpatient clinic of the vascular surgeon, who are planned for surgical or endovascular revascularization and who meet the in- and exclusion criteria are asked to participate in the study. In addition, their primary IC will also be requested to take part in the study. A primary IC is defined as follows: the person most involved in caring for the CLTI patient and supporting at least one instrumental activity of daily living of the patient or defined as the contact who supports in decisions by the patient. Patients can still be included, if their primary IC refuses participation. However, primary ICs can only be included together with a patient.

At the outpatient clinic information about the POCI-study is provided by a VNP or researcher and patients and ICs receive an information folder. They are called by telephone the next day by a researcher or VNP to ask if they want to participate. If so, oral informed consent will be obtained by the researcher or VNP and patients are randomized immediately upon inclusion, either into the prehabilitation group or the control group, the latter receiving the standard of care. Their IC will automatically be randomized to the same group. Within a few days all patients undergo a general health screening by a VNP or researcher and a blood sample will be taken as part of the standard care. Written informed consent will be obtained during this visit. Afterwards patients receive three questionnaires: the WHOQoL-BREF, the EQ-5D-5L and the iMTA Medical Consumption Questionnaire (iMCQ) (t=0). ICs are also asked to fill in two questionnaires: the WHOQoL-BREF, and the CSI (t=0). Afterwards, patients randomized into the intervention group are referred to the prehabilitation program where they are assessed by a physiotherapist and if indicated also a geriatrician, dietician or a quit smoking coach. The prehabilitation program will take two weeks, considering both the time needed to possibly reach significant results with the program and the time in which treatment is planned and must take place.

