### 8.2 Randomisation, blinding and treatment allocation

Randomization will be performed immediately after inclusion of a participant, either by the VNP or by the responsible researcher. Participants will be allocated to either the prehabilitation group or the control group. A variable block randomization procedure will be applied to minimize the risk of unequal group sizes and to reduce predictability of assignments. To further ensure comparability between study arms, randomization will be stratified by the participating hospital (to eliminate possible differences between hospitals). By stratifying we aim to prevent systematic imbalances and to enhance the internal validity of the trial. The randomization procedure will be carried out using the validated electronic data capture system Castor EDC. This study is not subject to blinding due to the extensive and active nature of the intervention. While blinding is not feasible, objective outcome measures and standardized assessment procedures will be used to minimize potential bias.

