## 10. STATISTICAL ANALYSIS

Statistical analyses are performed using IBM SPSS statistical software (SPSS Inc., Chicago, Illinois, USA). A two-sided p-value of less than 0.05 will be considered statistically significant. Adjusted analysis with prognostic baseline characteristics (e.g. gender, age) will be performed using regression analysis. This analysis corrects for baseline differences, optimizes statistical power, and provides better individualized treatment effect estimates. Missing data will be studied for specific patterns of occurrence, and multiply imputed. A power analysis with sample size calculation is performed, as described in paragraph 4.4 (sample size calculation).

Results of categorical data variables are described in frequencies with percentages and differences will be tested using the Chi-square test. Continuous data are described as median (interquartile range) and Mann-Whitney U-tests will be performed to test for group differences. Ordinal variables will be tested using the Mann-Whitney U-test. Data analysis will be done according to the intention-to-treat concept, which implies that all patients are included in the analysis irrespective of whether they completed the prehabilitation program. Secondary, a per protocol analysis will be performed, although interpretability may be difficult for this analysis. All epidemiological issues and statistical methods will be discussed with [name]. [name], a member of the research group.

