Lastly a cost-effectiveness analysis will be performed. The economic evaluation will include a cost analysis from hospital perspective, a cost-utility analysis from societal perspective (CUA, i.e. costs per QALY), and a budget impact analysis (BIA). In all three analyses, care with and without prehabilitation will be compared according to intention to treat. For the hospital cost analysis, 6 months interventions and stay will be assessed from the financial records of the Amphia Hospital, Meander Medical centre and Elisabeth TweeSteden hospital. For the CUA, also costs outside the hospital will be included, such as wound care, physiotherapy, home care, and informal care. These will be assessed using shortened versions of the iMCQ questionnaire (filled out at 6 months, over the preceding six months). Care will be valued according to Dutch reference prices, including travel costs. Productivity costs will not be included, because of the low labor participation in this 65+ study population. QALYs will be calculated using the Dutch tariff for the five-level EuroQoL EQ-5D (assessed at 0, and 6 months), with a sensitivity analysis using the EuroQoL visual analogue scale. Incremental average 6 months costs and QALYs will be compared using net-benefit analysis, with multiple imputation to account for missing data. The BIA will estimate the financial impact of different implementation scenarios at the national level. The analysis will be conducted from the perspectives of society, hospital and insurers, using the ZonMw BIA tool. The BIA will be based on the costs as estimated during the study, and the expected numbers of patients in the Netherlands. Healthcare will be valued according to cost prices (for the societal perspective) or NZa prices (for the hospital and insurer perspectives). Costs will be estimated per 1-year budget period for a time horizon of 5 years, assuming 50% to 100% implementation after 4 years.

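### The cost-utility comparison states no baseline adjustment, and no section names t=0 EQ-5D-5L utility or t=0 iMCQ cost as a covariate, so the incremental QALY may be estimated less precisely than the collected data allow

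*Protocol*

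**What the plan says.** The economic paragraph of protocol section 10.2 is fairly detailed. It sets out the perspectives, the tariff, a sensitivity analysis with the visual analogue scale, and the comparison principle: "care with and without prehabilitation will be compared according to intention to treat". On the outcome it says: "QALYs will be calculated using the Dutch tariff for the five-level EuroQoL EQ-5D (assessed at 0, and 6 months". On the comparison it says: "Incremental average 6 months costs and QALYs will be compared using net-benefit analysis, with multiple imputation to account for missing data". It lists no covariates and does not refer to the regression models described just before it.

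Baseline values exist. Under section 3, patients receive "the WHOQoL-BREF, the EQ-5D-5L and the iMTA Medical Consumption Questionnaire (iMCQ) (t=0" before the intervention group is referred to the programme. The economic paragraph, however, uses only the later iMCQ, "filled out at 6 months, over the preceding six months". No use is stated for the t=0 form.

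Two general rules are relevant:

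- Chapter 10 opens with "Adjusted analysis with prognostic baseline characteristics (e.g. gender, age) will be performed using regression analysis" and gives the reason: "This analysis corrects for baseline differences, optimizes statistical power, and provides better individualized treatment effect estimates".
- The first part of 10.2 promises covariate correction and hospital site as a factor for the secondary outcomes that it lists. Cost-effectiveness is not in that list, although section 8.1.2 counts it among the secondary outcomes.

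Both covariate lists are open-ended. Neither names t=0 utility or t=0 cost.

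**The concern.** A QALY built from two utilities contains the baseline utility as one of its two components. That baseline is measured before the programme starts, so a difference between arms in it cannot be an effect of the programme. In a plain difference of means it is nevertheless counted as QALYs gained or lost. It counts directly through the area under the curve, and again through its correlation with the 6-month utility.

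At stake is the width of the interval around the incremental QALY, and how far the point estimate depends on which arm happened to start with better utility. Chapter 10's own reasons for adjusting, namely baseline differences and power, apply with particular force to this outcome. If the covariates are left open until the economic data are seen, the choice between an adjusted and an unadjusted result can also be made after the fact.

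**Working it through.** The protocol gives no SD, correlation, standard error or power for the QALY comparison, so there is no stated figure to reproduce.

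**Inputs from the protocol.** Two EQ-5D-5L measurements, at 0 and 6 months (10.2). 300 patients in total (4.4), taken as 150 per arm.

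**Assumed inputs.** Linear interpolation. Utility SD s = 0.25 at t=0 and among survivors at 6 months. Correlation rho from 0.2 to 0.7. 6-month mortality m from 0 to 20%, with utility 0 at 6 months for deaths, deaths independent of u0, and a survivor mean of 0.60.

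**Step 1, the outcome.** QALY = 0.5 x (u0 + u6)/2 = 0.25 x (u0 + u6). The multiplier cancels from the ratios below.

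**Step 2, no deaths, equal SDs.**
- Unadjusted variance per patient: 0.0625 x s² x (2 + 2 rho).
- Variance after linear adjustment for u0: 0.0625 x s² x (1 - rho²).
- SE ratio, unadjusted over adjusted: sqrt(2/(1 - rho)).

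**Step 3, with deaths.**
- Var(u6) = (1 - m)s² + m(1 - m) x 0.60².
- Cov(u0, u6) = (1 - m) x rho x s².
- SE ratio = sqrt{[s² + Var(u6) + 2 Cov] / [Var(u6) - Cov²/s²]}.

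Example, m = 0.10 and rho = 0.5: Var(u6) = 0.05625 + 0.0324 = 0.08865 and Cov = 0.028125. The ratio is sqrt(0.2074/0.0760) = 1.65.

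| Survivor rho | No deaths | 10% deaths | 20% deaths |
|---|---|---|---|
| 0.2 | 1.58 | 1.42 | 1.34 |
| 0.3 | 1.69 | 1.48 | 1.39 |
| 0.5 | 2.00 | 1.65 | 1.50 |
| 0.7 | 2.58 | 1.90 | 1.65 |

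For rho 0.3 to 0.7 the range is about 1.4 to 2.6. The corner with rho 0.2 and 20% deaths falls slightly below it. Unequal SDs also move the ratio: with no deaths and rho 0.5, it is 2.25 if the 6-month SD is 0.8 times the baseline SD, and 1.68 if it is 1.5 times.

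**Step 4, absolute size (s = 0.25, rho = 0.5, no deaths).**
- Unadjusted SE: 0.25 x 0.25 x sqrt(3) x sqrt(2/150) = 0.0125.
- Adjusted SE: 0.25 x 0.25 x sqrt(0.75) x sqrt(2/150) = 0.0063.
- SE of the chance difference in u0: 0.25 x sqrt(2/150) = 0.029. One SE puts 0.25 x 0.029 = 0.0072 QALY directly into the increment.

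**Step 5, net benefit (illustration only).** Take the Step 4 inputs, and assume a cost SD of EUR 10,000, costs uncorrelated with QALYs, and adjustment of the QALY part only. Per patient, the QALY SD is 0.0625 x sqrt(3) = 0.108 unadjusted and 0.0625 x sqrt(0.75) = 0.054 adjusted. At lambda euros per QALY, the SE ratio is sqrt{[(0.108 lambda)² + 10,000²] / [(0.054 lambda)² + 10,000²]}. That gives about 1.02, 1.10 and 1.21 at EUR 20,000, 50,000 and 80,000 per QALY.

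**The case against.** The strongest reply is that the economic paragraph never says the comparison is unadjusted. A reader might infer from its silence that no adjustment is planned. The protocol does not support that inference: chapter 10 opens with a general policy of adjusted regression, and the economic paragraph closes the same section that corrects secondary outcomes for covariates and site. What can be said is that the paragraph does not state whether those rules apply. Even if they do, t=0 utility and t=0 cost are not named. The mixed models for repeated measures in 10.2 do not fill the gap either, because a QALY is one value per patient.

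A second reply is that the covariates of a net-benefit model are often left to an analysis plan or health-economic plan, which is not at hand. This limits the weight of the point. It does not remove it, because the protocol has already fixed the comparison in some detail and left out the covariate that matters most for this outcome.

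Third, hospital. One might infer that between-hospital differences are ignored. That is weak: the 10.2 site rule may be meant to cover costs too, and "randomization will be stratified by the participating hospital", so the arms should be nearly balanced on hospital.

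Fourth, randomisation keeps the unadjusted contrast unbiased on average, and its confidence interval already includes chance imbalance in u0. In the Step 4 example the 95% range of that direct carry-over, 1.96 x 0.0072 = 0.014, lies within the unadjusted half-width of 1.96 x 0.0125 = 0.0245 and is not additional to it. This stands in full.

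**Conclusion.** The point holds as a gap in specification with a real cost in precision. The economic comparison states no baseline adjustment, no section names t=0 utility or t=0 cost as a covariate, and it is unclear whether the general rules reach this analysis. If it is run unadjusted, the standard error of the incremental QALY is about 1.4 to 2.6 times what adjustment for t=0 utility would give. This rests on linear interpolation, equal utility SDs among survivors, a correlation of 0.3 to 0.7 and mortality of 0 to 20%, all assumed.

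Two stronger readings should be avoided. A flat statement that the standard error doubles needs a correlation near 0.5, equal SDs and no deaths; deaths at 6 months bring the ratio down. Nor does the QALY figure carry over to net benefit, which also contains cost variance. The protocol gives nothing to size the gain there or for costs, and it may be much smaller. There is no systematic bias from the lack of adjustment.

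**What to change.** Add one sentence to the economic paragraph of 10.2, for example: *Incremental QALYs, costs and net benefit will be estimated by regression on treatment arm within each imputed data set, adjusted for t=0 EQ-5D-5L utility (QALYs and net benefit), t=0 iMCQ cost (costs and net benefit) and hospital site.* Including site matches the rule already given for the other secondary outcomes. The change needs no new data and no new patients, and it gives the t=0 iMCQ a stated use. It should be settled before economic data are compared by arm.

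One small downside should be noted. The t=0 forms are completed after allocation is known, in an unblinded trial. If knowing the allocation shifts only the reported u0, by d between arms, the unadjusted QALY difference is biased by 0.25 x d. The adjusted one is biased by 0.25d - 0.25(1 + slope)d = -0.25 x slope x d, where slope is that of u6 on u0. The adjusted bias has the opposite sign and is smaller when the slope is below 1.

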### **10.3 Other study parameters**

Not applicable.

### **10.4 Interim analysis (if applicable)**

Interim analysis for the meetings of the DSMB shall be focused on the question if the complication ratio is not increased in the non prehabilitation group compared to the prehabilitation group.

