#### 8.1.2 Secondary study parameters/endpoints

Secondary outcomes (Appendix 1-Uitkomstmaten) will be postoperative complications, hospital readmission rate, 6-month mortality, QoL of both patient and their informal caregiver (measured by using the WHOQoL-BREF), the health related QoL of patients (measured by using the EQ-5D-5L), burden on informal caregiver (using the CSI), the level of perceived SDM of the patient and their IC (using the CollaboRATE), perceived and preferred roles in DM of the patient and their IC (using the ACPS), preferred participation in SDM of the patient and their IC (using the PICS), a cost-effectiveness analysis will be performed (using the iMCQ) and a process evaluation will take place (using an effect evaluation form designed by the research group). For the forms used to measure these endpoints, see 'F1-Vragenlijsten.

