### **8.7 Premature termination of the study**

This study will be terminated prematurely in case of any remarkable negative effects (complications and/or mortality) in the intervention group, compared to the control group.

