#### 9.2.2 Serious adverse events (SAEs)

A serious adverse event is any untoward medical occurrence or effect that

- results in death;
- is life threatening (at the time of the event);
- requires hospitalisation or prolongation of existing inpatients' hospitalisation;
- results in persistent or significant disability or incapacity;
- is a congenital anomaly or birth defect; or
- any other important medical event that did not result in any of the outcomes listed above due to medical or surgical intervention but could have been based upon appropriate judgement by the investigator.

An elective hospital admission will not be considered as a serious adverse event.

All events will be reported by the investigator to the sponsor. Patients will still be included in our database and will not be withdrawn from this study in case an adverse event occurs. To our knowledge, no other adverse events might occur when participating in this study.

The sponsor will report the SAEs through the web portal ToetsingOnline to the accredited METC that approved the protocol, within 7 days of first knowledge for SAEs that result in death or are life threatening followed by a period of maximum of 8 days to complete the initial preliminary report. All other SAEs will be reported within a period of maximum 15 days after the sponsor has first knowledge of the serious adverse events.

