### **9.4 Data Safety Monitoring Board (DSMB) / Safety Committee**

An independent DSMB will be established. The members of the DBMS will be:

- [name]. [name], vascular surgeon, Erasmus Medical Center
- Dr. [name], epidemiologist, Amphis Hospital
- [name], scientific advisor/monitor, Amphia Hospital

None of the members are otherwise involved in the study and the members have no conflict of interest with the trial. The DSMB will assess the safety of the tested prehabilitation component during the trial. Interim analysis for the DSMB meetings shall be focused on complications. Data will be presented as a percentage.

Based on this data, the DSMB will recommend one of the following actions:

- No action needed, trial continues as planned
- Proposing protocol changes
- Early stopping due to safety concerns

The advice(s) of the DSMB will only be sent to the sponsor of the study. Should the sponsor decide not to fully implement the advice of the DSMB, the sponsor will send the advice to the review committee, including a note to substantiate why (part of) the advice of the DSMB will not be followed.

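### Section 10.4 states the interim safety question in the reverse direction, contradicting 8.7 and 9.4, and the interim focus on complications omits the mortality that 8.7 names

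*Protocol*

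**What the plan says.** Four parts of the protocol bear on interim safety.

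- Section 10.4 sets the question for the DSMB meetings. The interim analysis is "focused on the question if the complication ratio is not increased in the non prehabilitation group compared to the prehabilitation group".
- Section 8.7 says that the study will be ended early "in case of any remarkable negative effects (complications and/or mortality) in the intervention group, compared to the control group".
- Section 9.4 sets the board's remit: "The DSMB will assess the safety of the tested prehabilitation component during the trial". On content it says: "Interim analysis for the DSMB meetings shall be focused on complications. Data will be presented as a percentage". One of the three possible recommendations is "Early stopping due to safety concerns".
- Section 8.1.2 lists complications and mortality as separate outcomes: "Secondary outcomes (Appendix 1-Uitkomstmaten) will be postoperative complications, hospital readmission rate, 6-month mortality".

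Section 9.2.1 has all adverse events during the study recorded. Section 9.2.2 counts as serious any event that "results in death", and has fatal and life-threatening SAEs reported to the ethics committee within 7 days. It does not name the DSMB as a recipient. Sections 8.4 and 8.6 keep collecting mortality and complications after a participant withdraws.

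**The concern.** Prehabilitation is the component under test, so an interim safety look should ask whether it does harm. Section 10.4 asks instead whether the arm without it does worse. Read literally, an excess of complications among control patients, which is what the trial hopes to find, is the result to watch for, and an excess among prehabilitation patients answers the question reassuringly. This is the only interim question that the protocol states, so a DSMB charter or analysis plan must either carry the reversal forward or contradict the protocol.

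The second issue is coverage. Section 8.7 rests on complications, mortality or both, but the interim content in 9.4 and 10.4 names complications alone. As written, nothing ensures that the board sees the mortality comparison on which early termination may depend.

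**Working it through.** **Is there a figure to reproduce?** No. Section 10.4 gives no look time, number of patients, test or threshold. The check is a comparison of texts.

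**Step 1: direction and outcome, side by side.**

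| Section | Group watched for an excess | Compared with | Outcomes named |
|---|---|---|---|
| 8.7 | Prehabilitation | Control | Complications and/or mortality |
| 9.4 | Safety of prehabilitation (remit) | Not stated | Complications, as percentages |
| 10.4 | Non-prehabilitation (control) | Prehabilitation | Complications |

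Sections 8.7 and 9.4 point the same way. Section 10.4 points the other way. Section 8.7 is the only one of the three that names mortality.

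**Step 2: what each rule answers.** Section 4.4 gives planning rates for control versus prehabilitation of 26% versus 14% (minor complications) and 23% versus 18% (major).

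- *The program works as planned.* Control minus prehabilitation is 26 − 14 = 12 points (minor) and 23 − 18 = 5 points (major). Literal answer to 10.4: complications are increased in the non-prehabilitation group. Under 8.7 there is no negative effect in the intervention group.
- *The program harms (assumption: the same rates, swapped).* Control minus prehabilitation is 14 − 26 = −12 points (minor) and 18 − 23 = −5 points (major). Literal answer to 10.4: complications are not increased in the non-prehabilitation group. Under 8.7 this is the kind of difference that bears on early termination.

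In both cases the literal answer to 10.4 is the opposite of what 8.7 needs.

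**Step 3: does the interim content cover 8.7?** Section 8.1.2 lists postoperative complications and 6-month mortality as distinct outcomes, so a table of complications cannot be assumed to contain deaths. Section 9.2.2 sends deaths to the ethics committee as individual reports, not to the DSMB as a comparison of arms. The mortality part of 8.7 therefore has no stated counterpart in the interim tables.

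**Step 4: are the missing data available?** Yes. Sections 8.4 and 8.6 collect mortality from the patient records, including for withdrawn participants, and sections 9.2.1 and 9.2.2 record AEs and SAEs.

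**The case against.** **The DSMB would see harm anyway.** This largely stands. The remit in 9.4 points in the right direction and includes advice to stop early. Complication percentages shown for both arms reveal an excess on either side, and setting a focus does not exclude other data. AEs and SAEs are recorded throughout the study, so deaths before surgery are captured. A reader might infer that harm from prehabilitation would not be examined, or that 8.7 could not be applied to mortality. The documents support neither: mortality is collected, and 8.7 does not depend on the DSMB's interim analysis. What remains is that the stated question is reversed and that by-arm deaths and SAEs for the board are not mentioned.

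**The direction may be deliberate.** Prehabilitation is already part of standard care at one of the three hospitals (Dutch summary; section 11.5), so controls there forgo existing care and might merit monitoring. Section 10.4 gives no such reason, and this reading would still leave it at odds with 8.7 and 9.4. The argument does favour wording that covers both directions.

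**Limb loss and waiting.** A reader might infer that amputations, or events before revascularization, are left out of safety monitoring. That goes too far. Appendix 1, which defines the outcomes, is not shown and may count amputation as a complication. Section 3 says that the program runs alongside treatment planning without delay, and section 4.3 excludes patients who need urgent intervention. The interim text simply does not name these events.

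**Table content belongs in a charter.** This is fair for layout and detail. It does not resolve a contradiction within the protocol.

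**Conclusion.** The concern holds in a limited form. Section 10.4 states the interim safety question in the reverse direction and contradicts 8.7 and 9.4. The interim content in 9.4 and 10.4 is also narrower than 8.7, because it omits mortality and does not say that the DSMB receives deaths or SAEs by arm.

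The first part rests on the wording alone. The second rests on the text shown; a DSMB charter or Appendix 1 could add detail. No probability of a missed or false signal can be given, because the protocol fixes neither the time of the look nor a trigger. The intent is largely clear from 8.7 and 9.4, and a careful board would probably act on it. Even so, the trial's only stated interim safety question should not depend on the board disregarding its wording. It should be corrected before the first DSMB meeting.

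**What to change.** 1. Reconcile 10.4 with 8.7 and 9.4. Reword it to ask whether the complication rate is increased in the prehabilitation group compared with the control group. If monitoring of controls is also wanted, ask whether the rates differ in either direction.
2. In 9.4 and 10.4, add deaths and SAEs by arm to the complication percentages, counted from randomisation in all randomised patients, so that the tables match 8.7. The all-randomised basis matters because 8.4.1 removes patients who refuse the program, which can happen only in the intervention arm.
3. State in the same place, or by reference to Appendix 1, whether limb loss and events before revascularization are included in the interim tables.

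The cost is a reworded sentence in 10.4, a sentence or two in 9.4, and the same wording in any DSMB charter. Deaths and SAEs need no new data collection, and the sample size and primary analysis are unaffected.
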